**Figure 1 F1:**
[figure not shown]
approach to the present study

**Table 1 T1:** the stage of the tumor will be determined by TNM staging TNM Classification based on AJCC 8^th^ edition

Stage 0	Tis	N0	M0
**Stage I :**	T1 - T2	N0	M0
**Stage IIA :**	T3	N0	M0
**Stage IIB :**	T4a	N0	M0
**Stage IIC :**	T4b	N0	M0
**Stage IIIA :**	T1 - T2	N1/N1c	M0
	T1	N2a	M0
**Stage IIIB :**	T3 - T4a	N1/N1c	M0
	T2 - T3	N2a	M0
	T1 - T2	N2b	M0
**Stage IIIC :**	T4a	N2a	M0
	T3 - T4a	N2b	M0
	T4b	N1-N2	M0
**Stage IVA :**	Any T	Any N	M1a
**Stage IVB :**	Any T	Any N	M1b
**Stage IVC :**	Any T	Any N	M1c

**Table 2 T2:** evaluation of expression of Ki-67 in colorectal carcinoma on Immunohistochemistry [4]

Immunoreactivity intensity scores	Immunoreactivity extent	Final score (immunostaning intensity x % of positive cells)
**Negative (0)**	<5% (0)	Negative Expression (-,0)
**Mild (1)**	6% to 25% (1)	Weak Positive Expression (+,1 - 3)
**Moderate (2)**	26% to 50% (2)	Moderate Positive Expression (+, 4 - 7)
**Strong/Intense (3)**	51% to 75% (3), 75% to 100% (4)	Strongly Positive Expression (+, 8 - 12)

**Table 3 T3:** evaluation of expression of HER2 in Colorectal carcinoma on Immunohistochemistry [11]

Immunohistochemistry staining	Immunohistochemistry expected pattern	Immunohistochemistry classification
**No staining (0)**		Negative (-)
**Faint staining (1+) any cellularity**	Segmental or granular	Negative (-)
**Moderate (2+) in <50% of cells**	Any	Negative (-)
**Moderate (2+) in ≥50% of cells**	Circumferential, basolateral or lateral	Equivocal
**Intense (3+) in ≤10% cells**	Circumferential, basolateral or lateral	Negative (-)
**Intense (3+) in >10% <50% of cells**	Circumferential, basolateral or lateral	Positive (+)
**Intense (3+) in ≥50% of cells**	Circumferential, basolateral or lateral	Positive (+)

**Grossing techniques for colon and rectum specimen** [8]: surgery is the main stay of treatment of colorectal carcinoma. TNM staging of tumour is a major prognostic factor which helps decide further management. Derivation of TNM staging is entirely dependent upon a meticulous examination and appropriate sampling of surgical specimen by the pathologist (Table 1). 1) Unopened specimens in formalin were received along with proper clinical history. The specimens were checked for identification; 2) the nature of the surgical procedure was noted; 3) the length of the entire specimen was recorded; 4) palpation of the tumour was carried out on the outer aspect of the specimen; 5) the quality of total mesorectal excision before application of ink or opening the APR and AR specimens was assessed; 6) both aspects of specimen photographed for records purposes; 7) tumour site perforation looked for before inking; 8) the non-peritonealised surface was painted with ink with special reinforcement to the NPS related to the tumour. It is adviced to not paint the serosa; 9) upon being inked, the specimen should be opened from the anterior aspect starting from either ends of the tumor to 1 cm above and below the tumor; 10) the distances of both longitudinal resection margins from the tumour are noted; 11) the location of tumour was recorded with relation to the anterior peritoneal reflection in the rectosigmoid, AR and APR specimens; 12) the entire specimen was fixed in appropriate volume of formalin over the course of 48 hours; 13) upon adequate fixation, sample longitudinal mucosal resection margins; 14) document the size of tumour in two dimensions; 15) sample appropriate parts of the tumor as described above and submit for microscopy; 16) all lymph nodes were dissected and submitted; 17) examine the rest of the bowel segment for any abnormality; 17) mesorectum/peri-colonic fat was sampled; 18) sections to be taken; 19) four or five sections of the tumour, all inclusive of serosa and/or CRM; 20) all lymph nodes dissected off the specimen and submitted according to the level of the tumour; 21) longitudinal mucosal resection margins; 22) adjacent mucosa; 23) sample from any other grossly abnormal area.

**Materials**: a) the study will include approximately 60 resected specimens from confirmed and planned Colectomy specimen received in the Department of General Pathology, J.N.M.C; b) formalin fixed, paraffin embedded blocks of tumor masses from resected Colectomy specimens; c) 10% formalin; d) grossing instruments (grossing tray, knife, scalpel, measuring tape, plain forceps, toothed forceps); e) automated tissue processing assembly; f) haematoxylin & Eosin stain; g) HER2 and Ki-67 marker; h) glass slides (Blue Star®). Dimensions: 7.5x 2.5 centimeters; i) binocular research microscope.

**Staining Protocol: haematoxylin and eosin staining** [9]: a) colorectal carcinoma sections are deparaffinized in xylene: Three 10-minute shifts; b) sections dewaxing is performed. Sections are rehydrated using progressively higher grades of alcohol; c) bring sections to water; d) in a jar, stain for 10 minutes with Harris hematoxylin; e) wash for 2-3 minutes under running water; f) for a few seconds, separate in 1 percent acid alcohol (1 percent HCl in 70% alcohol); g) alkaline water was used for 5 minutes; h) for 1 minute, stain in 1% aqueous Eosin; g) dehydrate through 90% alcohol; h) fount in Dibutylphthalate Polystyrene Xylene (DPX).

**Procedure for immunohistochemistry as given by manufacturer (path in situ)**: a) 3 mm portions to be incubated for 1 hour at 60-70O C on charged slides; b) for 15 minutes each deparafinze using xylene for twice; c) hydrate through descending grades of alcohol as follows: 1) absolute alcohol- 2 changes, five minutes each; 2) 90% alcohol- 5 minutes; 3)70% alcohol-5 minutes; 4) wash in distilled water, two changes, 2 minutes each; 5) antigen retrieval for 15 -20 mins in MERS. pH of retrieval buffer (6,8 or 9.5) as per the marker; 6) wash in distilled water, two changes, 2 minutes each; 7) wash in PBS /TBS for 2 minutes; 8) endogenous peroxidation is inhibited by administering H2O2 to the area for 5 minutes. Wash in the wash buffer for 2 minutes twice; 9) for 30 minutes, place the HER2/Ki-67 primary antibody in a moist chamber. Then, wash twice in the wash buffer for 2 minutes each; 10) keep the Polyexcel Target binder reagent for 12 minutes. Wash in two different buffers for two minutes each; 11) incubate Polyexcel HRP for 12 minutes. Wash with buffer for 2 minutes, then change; 12) add functioning DAB chromogen (1ml DAB Buffer + 1 drop DAB Chromogen, mix thoroughly) and leave for 2-5 minutes before washing in distilled water; 13) hematoxylin counterstain for 30 seconds, then rinse with water; 14) dehydrate (70, 90, and absolute), clear (xylene), and mount as standard.

## Discussion

### Methodology of Interpretation

**Interpretation based on histologic grade** [10]: a variety of colorectal cancer grading systems have been proposed, however there is no single generally acknowledged and regularly utilised grading criteria. Most tumours are classified into three or four grades: a) Grade 1 (G1) - Well-differentiated; b) Grade 2 (G2) - Moderately differentiated; c) Grade 3 (G3) - Poorly differentiate; d) Grade 4 (G4) - Undifferentiated.

Despite high interobserver heterogeneity, multivariate analysis has repeatedly demonstrated that histologic grade is a stage-independent predictive predictor. High tumour grade, in particular, has been shown to be a poor predictive factor. The use of a two-tiered grading system for colorectal cancer is recommended in view of its established predictive efficacy, relative simplicity, and consistency. The following grading standards are proposed based only on gland development. A) low grade: >/= 50% gland formation; b) high grade: < 50% gland formation.

**Statistical analysis:** it will be carried out by ‘chi square test’ by analyzing the relationship of Ki-67 and HER2 protein expression in colorectal carcinoma. Multiple linear regression analysis is performed to determine the relative elements that contribute to metastasis. A value of P <0.05 considered to indicate statistical significance.

**Scope**: due to its high prevalence and mortality rate, colorectal cancer (CRC) has evolved into a global issue for public health. Immunohistochemical analysis and protein markers such as HER2 and Ki-67 are now being used to enhance the identification of individuals who are more likely to have a poor clinical outcome and hence benefit from early detection.

**Limitations**: 1) inter-observer and intra-observer variability; 2) technical errors while processing can influence the interpretation of immunostaining.

**Observation and results**: they will be collected and combined together over the period of two years and will be analyzed statistically.

**Trial registration number:** this study is registered with the Clinical Trials Registry - India (CTRI) and the Trial number is CTRI/2023/05/053165.

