## Introduction

Colorectal carcinoma (CRC) is one of the most prevalent malignancies globally, and it is the fourth leading cause of cancer-related death. CRC incidence rates vary greatly, with roughly 60% of cases identified in wealthy nations. The switch to a more Western diet has been linked to an increase in cancer rates in emerging nations [1]. In 2020, CRC will account for 10% of global cancer incidence and 9.4% of cancer-related deaths, trailing only lung cancer, which will account for 18% of fatalities. According to projections of population growth, ageing, and human progress, the global number of newly diagnosed CRC cases is predicted to reach 3.2 million by 2040.Based on projections of ageing, population expansion, and human progress, the worldwide number of new CRC cases is expected to reach 3.2 million by 2040 [2]. The majority of Indian research show that these tumours occur in people aged 45 to 84, with a male preponderance. The most likely locations for carcinomas are the rectum and sigmoid colon. Carcinoma is a malignant neoplasm of epithelial origin or a cancer originating from internal and external lining of the body. All cancers of the large intestine (colorectal cancer) originate from the cecum to the anus. Colon cancer, which extends from the cecum to the sigmoid (about 15 cm above the anal margin), and rectal cancer, which extends from the recto-sigmoid to the anus, are the two types of colorectal cancer. CRC originates as a benign polyp on the inner lining of the colon or rectum [3]. Unfavorable stressors like obesity, calorie rich diet, and diet devoid of fibre, minimal physical activity, cigarette smoking, and alcohol consumption, in addition to an ageing population in high-income nations, epithelial cells are exposed for a lengthened transit time. As a consequence, colorectal epithelium will be more susceptible to the impact of mutagenic compounds, thereby increasing cancer risk [4]. Patients may have a variety of signs and symptoms, including occult overt rectal bleeding, bowel changes, anaemia, or abdominal discomfort. Individuals over the age of 45 should have a colonoscopy if they experience rectal bleeding. CT colonography or MRI abdomen and pelvis are complimentary imaging methods for the diagnosis of colorectal cancer. MRI is used to do locoregional staging in rectal cancer. PET-CT imaging is also being used. The Tumour, node and metastasis (TNM) and American Joint Committee on Cancer classifications are used to predict the prognosis of newly diagnosed colorectal cancer (CRC) (8^th^ edition). Tumor extent, lymph node status, tumour grade, and lymphatic and venous invasion evaluation remain the major morphological prognostic variables. Tumor budding and tumour border configuration are crucial additional histological markers, however they are not considered critical in prognosis [5]. The availability of monoclonal antibodies against the vascular endothelial - and epidermal growth factor receptor has recently boosted the therapeutic arsenal. In mCRC, preclinical and clinical trials of Anti-HER2 targeted therapy have shown promising results. Because of the high mortality rate in advanced metastatic cancer, it appears that improved detection procedures are necessary. The concept of antibodies attaching selectively to antigens in biological tissues to detect antigens in cells of a tissue segment is utilized in Immunohistochemistry (IHC). The antibody-antigen binding can be seen in a variety of ways. In histology, immunohistochemistry is used to identify the presence of a particular protein marker that can help with tumour categorization and diagnosis. ErbB-2 is a receptor tyrosine-protein kinase that is also known as HER2. The prognostic biomarker human epidermal growth factor receptor 2 (HER2) is utilised to detect tumoral tissues. The transmembrane receptor protein is present on all normal cells and is involved in a wide range of biological processes such as cell proliferation and apoptosis, differentiation, and cell migration [4]. HER2 protein overexpression or gene amplification has been associated with higher stage, positive lymph node status and tendency for poor overall survival. Ki-67 as a prognostic predictor for well-known cancers. It has been established that its expression is inextricably bound to cell growth. Ki-67 expression and proliferation activity appear to rise dramatically, and it is essential in the majority of cell cycle stages. Elevated expression of Ki-67 in CRC is related with a lower survival rate, carcinogenesis, and cancer cell metastasis, suggesting that Ki-67 might be used as a prognostic biomarker in CRC patients [4]. The current study proposes to investigate the status of Ki-67 and HER2 expression in colorectal carcinomas in connection to prognostic parameters such as histological type, grade, tumour size, and lymph node status. The objectives were a) to confirm already diagnosed colorectal carcinoma by histopathological examination; b) to determine histological grades of CRC based on histopathological prognostic markers;m c) to determine staging of colorectal carcinoma by TNM classification based on American Joint Committee of Cancer (AJCC); d) to asses HER2 and Ki-67 expression in tumor tissues of colon and rectum by immunohistochemistry; e) to compare Ki-67 and HER2 expression with histopathological prognostic markers and TNM staging.

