**Information sources**: the search will use sensitive topic-based strategies designed for each database. The search will be carried out in the following databases: Pubmed, Embase, Cinahl, Research Gate, Ajol, Google Scholar, Web of Science, Scopus and Cohrane Library. Only observational studies will be included.

**Search strategy**: ((“Colorectal Neoplasms”[MeSH] OR “Colorectal Carcinoma”[Text Word]) AND ("HER2"[MeSH] OR “HER2 Positive”[Text Word]) AND ("Ki-67 Antigen"[MeSH] OR “Ki-67”[Text Word]) AND ("Immunohistochemistry"[MeSH] OR “IHC”[Text Word]) AND ("Prognostic Markers"[MeSH] OR “Prognostic Factors”[MeSH] OR “Prognosis”[MeSH]) AND ("Histopathological Parameters"[MeSH] OR “Histopathology”[MeSH]) AND ("TNM Staging"[MeSH] OR “TNM Classification”[MeSH])).

**Sample size**: sample size calculation for a study estimating a population prevalence was described by Daniel in 1999. The calculation is intended to determine an adequate sample size to estimate the population prevalence with a good precision. The sample size calculation will be performed according to the formula suggested by Daniel.

$$\frac{{\left(Za/2\right)}^{2}*p*\left(1-p\right)}{d^{2}}$$

Where, “Z a/2” is the level of significance at 5% that is 95% confidence interval = 1.96 “p” is the prevalence of colorectal carcinoma = 0.2854 “d” is the desired error of margin = 7% = 0.07 “n” is the sample size. n = 1.96^2^x 0.2854 x (1-0.2854)/ 0.07^2^= 63.85 = Approximately 60-65 patients are needed in each study group. Study Reference: Consensus document for management of colorectal carcinoma by ICMR Formula Reference: (1999) Statistical formulas: Kappa statistics, Test statistics Software Used: SPSS 27.0 Version Level of study: Level III Sample Allocation: Random Selection of patients Study Design: Prospective Cross-sectional study.

**Approach to present study**: (Figure 1) the approach for the current study is detailed in the figure provided below. This figure outlines the step-by-step approach used in conducting the research and presenting the findings. It encompasses various stages of the study like determining the tumor staging using TNM (Table 1), Evaluation of expression of Ki-67 (Table 2) and HER2 (Table 3). This approach ensures transparency and clarity in how the study was conducted, facilitating reproducibility and reliability of the results.

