## Conclusion

The results of an IHC research employing HER2 and Ki-67 to identify HER2 and Ki-67 protein expression and correlate with histological prognostic indicators and TNM staging will be used to make conclusions.

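### The chi-square sentence names no grade, node or TNM variable, and an ordinary chi-square test ignores the order of the protocol's own scales, costing much of the power available with about 60 patients

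*Protocol article*

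**What the plan says.** The Introduction closes with the objectives. Objective (e) is "to compare Ki-67 and HER2 expression with histopathological prognostic markers and TNM staging". The Comparison item in Methods repeats this, and the Conclusion says that the expression results, used to "correlate with histological prognostic indicators and TNM staging will be used to make conclusions", are the basis for inference.

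Under Methodology of Interpretation, the Statistical analysis paragraph names a "chi square test", carried out "by analyzing the relationship of Ki-67 and HER2 protein expression in colorectal carcinoma". The same paragraph adds one model, "Multiple linear regression analysis is performed to determine the relative elements that contribute to metastasis", and a threshold, "A value of P <0.05 considered to indicate statistical significance". The Sample size paragraph also lists "Statistical formulas: Kappa statistics, Test statistics" without saying what kappa is for.

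The scales are defined elsewhere in the article. Table 2 gives Ki-67 four classes (negative, weak, moderate, strong) from a 0-12 product score. Table 3 gives HER2 three classes (negative, equivocal, positive). Table 1 lists 11 stage rows from 0 to IVC. Grade is described in four levels, with a two-tier version recommended. On numbers, the Materials paragraph says that "the study will include approximately 60 resected specimens".

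**The concern.** Two things in the sentence look wrong.

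First, read literally, it crosses the two markers with each other, which no listed objective asks for. The comparison that the study will draw conclusions from, each marker against grade, nodes and stage, has no test attached to it by name.

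Second, if the test is then applied to that comparison, it treats ordered categories as unordered labels. The prognostic hypothesis is directional: expression rises or falls as stage or grade worsens. A chi-square test of association spreads its sensitivity over every possible departure from independence, so little is left for that one pattern. With about 60 patients the likely result is a non-significant finding that is read as no relation between marker and stage, when the test had little chance of showing one.

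**Working it through.** **No figure to reproduce.** The article states no power or effect size for the chi-square test. Its only calculation is the prevalence-precision formula in the Sample size paragraph, which does not concern this test. (That formula gives 1.96² × 0.2854 × 0.7146 / 0.07² = 159.9 rather than the printed 63.85, which is a separate matter.) The check uses n = 60 from Materials.

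**Step 1: what is crossed with what.**
- Objective (e), the Comparison item and the Conclusion: each marker against histopathological parameters and TNM stage.
- Chi-square sentence: Ki-67 and HER2 expression, with no second variable named.
- Linear regression: metastasis as the outcome, so it does not supply the missing comparison.
- Kappa: a measure of agreement, with no stated use, so it does not supply it either.

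**Step 2: degrees of freedom.** For an r × c table an ordinary chi-square test has (r−1)(c−1) degrees of freedom; a linear-by-linear trend test has 1.
- Ki-67 (4) by stage I-IV (4): 3 × 3 = 9 against 1.
- HER2 (3) by stage I-IV (4): 2 × 3 = 6 against 1.

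**Step 3: power at n = 60, alpha 0.05.** The documents give no frequencies, so these are assumptions: Ki-67 10/25/35/30%; HER2 85/10/5%; stage I-IV 15/35/38/12%; grade 80:20. Two latent normal variables with the stated correlation are cut at these margins, and power is the share of simulated data sets with p < 0.05.

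| Table | Correlation | Chi-square | Trend test |
|---|---|---|---|
| Ki-67 by stage I-IV | 0.4 | about 39% | about 79% |
| Ki-67 by stage I-IV | 0.2 | about 11% | about 28% |
| HER2 by stage I-IV | 0.4 | about 28% | about 49% |
| HER2 by stage I-IV | 0.2 | about 9% | about 15% |
| Ki-67 by two-tier grade | 0.4 | about 29% | about 49% |

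A different model gives the same direction. With uniform margins and a common odds ratio per stage step, Ki-67 by stage I-IV has 54% against 89% at odds ratio 2, and 20% against 48% at odds ratio 1.5.

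The gain disappears when both variables are binary. With an assumed 50:50 by 35:65 split and correlation 0.4, both tests have 50%.

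**Step 4: sparsity and type I error.** Expected counts sum to 60, so at most 60/5 = 12 cells can reach 5.
- Ki-67 by 11 stage rows: 44 cells, mean 60/44 = 1.36; at least 44 − 12 = 32 cells (73%) fall below 5 whatever the margins.
- HER2 by 11 stage rows: 33 cells, mean 60/33 = 1.82; at least 33 − 12 = 21 cells (64%) fall below 5.

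Low expected counts do not by themselves mean a wrong error rate. Simulated type I error of chi-square at nominal 5% (margins as in Step 3; the split into 11 rows is also assumed):
- Ki-67 by stage I-IV: 4.6%.
- HER2 by stage I-IV: 5.1%.
- Ki-67 by HER2: 4.9%.
- Ki-67 by two-tier grade: 4.5%.
- Ki-67 by 11 rows: 4.0% to 5.1%.
- HER2 by 11 rows: 9.3% to 10.7%. If assumed HER2 positivity is varied from 3% to 30%, the range is about 8-12%. With uniform margins it is about 3%.

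The trend test on HER2 by 11 rows stays at about 5%.

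**The case against.** **The wording is loose rather than wrong.** The sentence can be read as each marker's relationship with tumour features, and three other places make the intended comparison clear. This stands. A reader might infer that the study will test the wrong question; the documents do not support that. What remains is that the sentence does not name the variable pairs.

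**The type of chi-square is not stated.** A linear-by-linear test is itself a 1-df chi-square statistic. True, but without qualification the term is ordinarily taken as the test of association, and nothing in the paragraph points to a trend version.

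**The chi-square test is not generally unreliable here.** A reader who sees 1.4 or 1.8 patients per cell might conclude that the p-values are invalid throughout. The simulations do not bear this out: only HER2 by all 11 rows is inflated, and some collapsed HER2 tables are conservative (about 2-4% when assumed positivity is 5% or less). Table 1 is a staging key, and nothing says that its 11 rows will be cross-tabulated.

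**Power depends on the assumptions.** This stands. At correlation 0.2 both tests are weak, and between two binary variables they are equal. The trend test still leads in every ordered table in Step 3 with more than two classes on at least one side.

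**Some details belong in a fuller plan.** Choice of main tests, multiplicity and exact-test fallbacks may be left there by an article. They are not part of this point.

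**Conclusion.** The point holds as one of specification and efficiency. The analysis sentence does not name the comparisons in objective (e), and the stated test ignores the order that the article's own scales carry. For Ki-67 by stage I-IV this roughly halves power, from about 79% to 39% at an assumed latent correlation of 0.4. For HER2 by stage I-IV it falls from about 49% to 28%. At correlation 0.2 the losses are 28% to 11% and 15% to 9%. These figures rest on assumed margins, n = 60 and a monotone association, none of which the documents supply apart from the approximate sample size.

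Three stronger readings are not supported:
- That chi-square is the only categorical statistic. Kappa is also listed, although without a purpose.
- That the chi-square approximation breaks down in general. Inflation, at about 9-11% under skewed assumed margins, is shown only for HER2 against uncollapsed stage.
- That the study intends a marker-against-marker test as its main analysis.

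**What to change.** Reword the Statistical analysis sentence so that it:
- tests Ki-67 and HER2 separately against each histopathological factor and TNM stage, naming the factors;
- groups stage as I-IV for testing, so that HER2 by all 11 rows is not tested with an asymptotic chi-square;
- uses an order-respecting test, linear-by-linear or Kendall tau-b, where the factor is ordered (grade, nodal category, stage);
- keeps chi-square, or an exact test, for nominal factors such as histological type.

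This costs a few sentences, no extra patients and no extra data. The statistical price is that a trend test is less sensitive to non-monotone patterns, for example expression peaking in middle stages, and that it gains little when both variables are nearly binary. Showing the full cross-tabulation beside each trend test lets a reader see such a pattern.
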